### Economic Evaluation Methods

The economic evaluation aims to estimate the cost-effectiveness of 10 kHz SCS plus usual medical care when compared to sham stimulation plus usual medical care. Healthcare resource utilisation, e.g. management of adverse events, interventions, investigations, medication, inpatient hospitalisations, Emergency Department and other health-care related visits, plus out-of-pocket costs and absences from work will be collected for each patient during the study follow-up period. Resources required for the implantation intervention will be recorded within the trial.

Items of resource use will be costed using national averages obtained from national sources (such as the Personal Social Services Research Unit, the British National Formulary and National Health Service (NHS) reference cost databases). Cost components will be combined to derive total patient level costs for the NHS. In addition, non-NHS costs such as productivity loss due to absence from work or patient out-of-pocket expenses will also be quantified to provide a full picture of how the strategies being compared will affect the financial burden imposed by the condition on both the NHS and the patients.

Generic health-related quality-of-life (HRQoL) data will be collected using the EQ-5D-5 L instrument. Both resource utilisation (costs) and EQ-5D-5 L will be collected at each follow-up visit. A within-trial cost consequence analysis will be carried out to estimate mean resource utilisation, costs, EQ-5D scores and total quality-adjusted life years (QALYs) in each group, together with relevant measures of sampling uncertainty. QALYs will be calculated using the area under the curve approach, with regression-based adjustment for the baseline EQ-5D score.

The economic evaluation will take the form of a cost-utility analysis to calculate the cost per additional QALY gained. Base-case analyses will be conducted from the NHS perspective, with additional analyses being conducted from the societal perspective. Deterministic and probabilistic sensitivity analysis will be undertaken to explore the robustness of the results to plausible variations in key assumptions and variations in the analytical methods used. Cost-effectiveness acceptability curves will be constructed to show the probability that the intervention is cost-effective at specific thresholds of cost per QALY gained. The analyst will be blinded to the group allocation.

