### Study Setting

Participants will be recruited from two neuromodulation centres: Guy’s & St. Thomas NHS Foundation Trust, London, UK, and South Tees Hospitals NHS Foundation Trust, Middlesbrough, UK.

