#### Allocation Concealment

Patients will be allocated 1:1 to intervention or control and were stratified by centre using a web-based computer-generated random-allocation sequence to ensure concealment. This website will be password protected and managed by Exeter CTU.

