#### Data Collection/Management

Data analyses will be conducted and reported in accord with CONSORT (Consolidated Standards Of Reporting Trials) guidelines for non-drug trials [28]. Participant flow will be summarised using a flow diagram, which will report recruitment and drop-outs and baseline patient characteristics and outcome scores reported and compared by group. The primary analysis for the primary and secondary outcomes will take an intention-to-treat approach based on a between-group comparison of intervention and control participants with complete data at 6 months, with adjustments being made for the baseline outcome score and centre. In a secondary analysis we will extend the primary analysis model with a repeated measures comparison of groups at all follow-up points. We comprehensively examine patterns and reasons for the missing outcome data and undertake appropriate imputation models to assess the impact of missingness on primary analysis models. Results will be reported for between-group mean differences and 95% confidence intervals. Safety outcomes will be reported descriptively by group. No correction of *P* values for multiplicity of testing will be undertaken. However, the primary outcome analysis will be performed before all other analyses, and the *P* values of all subsequent analyses will be interpreted in the context of multiple testing. No interim analyses are planned.

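### The QALY regression names baseline EQ-5D but not centre, although centre stratifies the randomisation and enters the model for the other outcomes: a small, conservative mismatch that one sentence would align

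*Protocol article*

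**What the plan says.** Four places in the protocol article bear on this.

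- **Study Setting:** "Participants will be recruited from two neuromodulation centres".
- **Allocation Concealment:** "Patients will be allocated 1:1 to intervention or control and were stratified by centre". The block structure is not stated.
- **Data Collection/Management:** the primary analysis of the primary and secondary outcomes compares groups at 6 months, "with adjustments being made for the baseline outcome score and centre".
- **Economic Evaluation Methods:** "QALYs will be calculated using the area under the curve approach, with regression-based adjustment for the baseline EQ-5D score". Mean costs and QALYs per group are to be reported "together with relevant measures of sampling uncertainty", with no covariate named for costs. Resource use is priced uniformly: "Items of resource use will be costed using national averages obtained from national sources". Sensitivity analyses will cover "plausible variations in key assumptions and variations in the analytical methods used".

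The Abstract lists EQ-5D-5L and costs among the secondary outcomes. The Secondary Outcomes section lists health-related quality of life and cost-effectiveness.

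**The concern.** An analysis should normally account for the factors used to stratify the randomisation. When allocation is balanced within centre, the difference between centres no longer contributes to the sampling error of the treatment contrast. A model without centre still counts that difference as residual noise, so its standard error overstates the true one.

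The model for the primary and secondary outcomes follows this principle. The QALY regression, as worded, does not: it specifies an adjustment and leaves centre out of it. For costs the text is simply silent.

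At stake is the reported precision of the incremental QALYs and costs. If their standard errors are overstated, the intervals are wider than the design delivers, and any acceptability curve built on those standard errors is drawn towards 50%. The analyst would also have two documented covariate sets to choose between for closely related outcomes.

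**Working it through.** **Sample size, to set the scale.** The plan gives no figure for the width of the cost-effectiveness interval. Its only related figure is the total of 96. The inputs in the Sample Size section are a 20 mm difference, SD 25 mm, 90% power, 5% alpha (taken as two-sided) and 30% attrition.

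- n per arm = 2 × (1.960 + 1.282)² × 25² / 20² = 32.8, so 33.
- 33 / 0.7 = 47.1, so 48 per arm and 96 in total. This reproduces the Abstract's total.
- Expected completers: 96 × 0.7 = 67.

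(The Sample Size section words the 96 as a per-group number, which conflicts with the Abstract. Only the total reproduces. This does not bear on the present point.)

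**Formula.** With two equal centres and arms balanced within centre, a model without centre reports a standard error too large by about

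1/√(1 − R²),

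where R² is the share of residual outcome variance that centre explains. For a centre difference d and residual variance v within centre, R² = (d²/4) / (v + d²/4).

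**Assumed range.** The documents give no centre effect on QALYs or costs, so d is varied on two scales:

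- residual scale: d in residual SDs, v = 1;
- total scale: d in outcome SDs with an assumed baseline correlation of 0.5, so v = 1 − 0.5² = 0.75.

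| d | R², residual scale | Excess SE | R², total scale | Excess SE |
|---|---|---|---|---|
| 0 | 0 | 0% | 0 | 0% |
| 0.3 | 0.022 | 1.1% | 0.029 | 1.5% |
| 0.5 | 0.059 | 3.1% | 0.077 | 4.1% |
| 0.8 | 0.138 | 7.7% | 0.176 | 10.2% |

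Example, total scale, d = 0.5: R² = 0.0625 / (0.75 + 0.0625) = 0.077, and 1/√0.923 = 1.041.

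**Simulation, total scale.** Two centres of 48, stratified 1:1, 30% attrition, 6,000 trials per setting:

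| d | SE ratio, without / with centre | Coverage without centre | Coverage with centre |
|---|---|---|---|
| 0.3 | 1.014 | 94.8% | 94.9% |
| 0.5 | 1.039 | 95.6% | 95.1% |
| 0.8 | 1.100 | 96.2% | 94.9% |

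At d = 0.8 with no attrition, the ratio was 1.103 and coverage without centre 97.3%.

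**Simulation, residual scale.** 68 completers (the nearest number to 67 that divides evenly into four cells), 8,000 runs per setting:

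- Balanced within centre, d = 0, 0.2, 0.5 and 1.0: mean standard error without centre 0.242, 0.243, 0.249 and 0.271, against about 0.242 with centre. Coverage without centre was 95.1%, 94.9%, 95.5% and 97.3%.
- Simple randomisation within centre, with no forced balance: coverage without centre was 94.8% to 95.3%. The interval is then valid. At d = 1.0 it is less precise (mean standard error 0.273 without centre, 0.245 with).

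**What the excess means.** A ratio of 1.10 understates the information by 1 − 1/1.10² = 17%; a ratio of 1.04 by 1 − 1/1.04² = 8%. If the acceptability curve is driven by net benefit divided by its standard error, and that standard error is inflated equally, the quotient shrinks by 1 − 1/1.04 = 4% or 1 − 1/1.10 = 9%.

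**Price of adjusting when centre has no effect.** About 0.2% on the standard error under stratified allocation with 30% attrition, and 0.246 against 0.244 (0.8%) with no forced balance.

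**The case against.** A reader might infer that QALYs will be adjusted for baseline EQ-5D alone, that costs will not be adjusted at all, and that the resulting intervals are therefore too wide. The documents do not support that.

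- **The text does not exclude centre.** The QALY sentence names one covariate without saying it is the only one, and nothing says that costs are unadjusted. Since EQ-5D-5L, costs and cost-effectiveness are secondary outcomes, the centre adjustment in Data Collection/Management can be read to reach them. This stands, and the cost part of the point does rest on silence. For QALYs, however, the sentence describes a regression adjustment and omits a factor that the general rule includes, so the wording is incomplete on either reading.
- **Detail belongs in the SAP.** The Statistical Methods section promises one, and an article need not list every covariate. That is fair for what is left unsaid. It does less for a covariate that is stated, because the SAP would inherit two specifications.
- **The excess width is conditional.** It needs a centre effect beyond baseline EQ-5D and balance within centre. Neither is given. Both centres share eligibility criteria and programming. This stands. National unit costs remove price differences between centres, though not differences in the amount of care used.
- **The effect is small and safe in direction.** This stands: up to 0.5 SD the excess is about 4% or less, and no bias follows when arms are balanced within centre.
- **Sensitivity analyses on methods are planned.** They leave the base case as it is.

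**Conclusion.** The point holds as a minor mismatch. The QALY regression, as worded, omits the stratification factor that the model for primary and secondary outcomes includes, and the cost analysis names no covariate.

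If the economic section is followed literally, if centre predicts QALYs or costs beyond baseline EQ-5D, and if arms are balanced within centre, the intervals for the increments would be somewhat too wide: roughly 0 to 4% for a centre difference of up to 0.5 SD, and about 8 to 10% at 0.8 SD depending on the scale. The centre differences, the baseline correlation of 0.5 and the within-centre balance are all assumptions. Without forced balance, the interval without centre keeps its nominal coverage and merely loses precision when centre matters.

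The protocol does not show that the cost-effectiveness intervals will in fact be too wide. Nor does it say how the acceptability curves are generated, so the effect on them is conditional too.

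**What to change.** Align the Economic Evaluation Methods section with the Data Collection/Management section. Suggested wording:

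*Incremental QALYs will be estimated by regression on treatment group with adjustment for baseline EQ-5D score and centre, and incremental costs by regression on treatment group with adjustment for centre. These adjusted increments and their joint uncertainty will feed the cost per QALY and the acceptability curves.*

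This uses a variable already held for the randomisation and takes one degree of freedom, from about 67 completers if attrition reaches 30%. It should be settled before any analysis, in the protocol or in the promised SAP, so that only one specification remains.

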### Statistical Methods

The trial statistician will be blinded to the group allocation and will undertake analyses using STATA. A detailed statistical analysis plan (SAP) will be prepared that will be presented to the Trial Steering Committee (TSC) and Data Monitoring Committee (DMC) for their review ahead of any analysis being undertaken.

### Data Monitoring

A joint Trial Steering Committee (TSC) and Data Monitoring Committee (DMC) will provide supervision for the trial, providing advice to the Chief and Co-investigators (Trial Management group [TMG]) on all aspects of the trial conduct and affording protection for patients by ensuring the trial is conducted according to the Medical Research Council (MRC) Guidelines for Good Clinical Practice in Clinical Trials. The TSC/DMC will be chaired by an academic clinician independent of the trial plus three other members plus the chief investigator, trial manager, statistician and health economist.

### Harms

#### Foreseeable Adverse Events and Anticipated Adverse Device Effects

We expect the risk of serious adverse events to be rare, and our results from the previous 10 kHz stimulation trial showed the risk of adverse events to be as follows:
Battery pocket pain 8%Wound infection 3%Electrode migration 5%Lead Fracture or malfunction 6%Headache from epidural puncture 1%Nerve injury < 1%Spinal cord haematoma and abscess < 1%Unwanted, perceived stimulation < 1%

Pocket pain is usually self-limiting within 6 months, and electrode migration is mitigated using cascade stimulation programming. Wound infection will necessitate the removal of the device. In some instances the system will require repair or removal. The reasons for this include infection, hardware displacement, pain or discomfort from the device, or device failure. The risks are similar to those mentioned above.

All adverse events will be recorded and reported in accordance with Good Clinical Practice.

#### Device Repair or Removal

Possibly, the SCS will need to be removed or repaired. Reasons include patient withdrawal from study, infection, hardware failure, lead migration, SCS related pain, allergy or other adverse reaction to device, or a required MRI scan.

If this occurs, the participant must consent to a further surgical procedure, and the surgical process is similar to that of implantation. With removal, all hardware will be removed, and with repair, the changes necessary to the SCS components will be determined by which component is unsatisfactory. The risk from these surgeries is similar to that of implantation, with a small risk that some of the components may not be safely removed. All such procedures will be done by the study implanter. Any adverse events are monitored and documented in the CRF.

### Auditing

The TSC will meet three times in the first year, twice in the second year and three times during the third year. The DMC will meet twice in the first year and annually thereafter.

If the chief and co-investigators are unable to resolve any concern satisfactorily, personal investigators, and all others associated with the study, may write to the chairperson of the TSC, through the trial office, drawing attention to any concerns they may have about the possibility of particular side-effects or about any other matters thought relevant. Interim analyses of recruitment rate, safety and outcome data will be supplied, in strict confidence, to the committee, along with any other analyses that the committee may request.

### Ethics and Dissemination

#### Declaration of Helsinki, International Standards and National Regulations

The clinical investigation shall be conducted in accordance with the ethical principles of the Declaration of Helsinki, ISO 14155, and all other applicable device and UK regulations.

Central ethical approval was provided by London-Camberwell St. Giles Research Ethics Committee for both centres, part of the NHS Health Research Authority. REC reference: 18/LO/1031, IRAS project ID: 232729. We will not begin recruiting at other centres in the trial until local ethical approval has been obtained. Informed written consent will be obtained prior to trial participation.

#### Protocol Amendments

Any protocol amendments will be discussed and approved within the TMG and presented to inform the TSC/DMC.

### Consent

The principal investigator or qualified designee will document the informed consent process, including the date of consent and name of the person conducting the consent process in the participant’s medical record. Individuals will be considered enrolled in the study once they have signed the informed consent form (Additional file 1). On the consent form, participants will be asked if they agree to the use of their data by responsible and designated individuals in the Foundation trust and regulatory authorities, the Exeter CTU and other collaborators. Participants will also be asked for permission to be contacted about future research projects, where relevant. This trial does not involve collecting biological specimens for storage.

### Confidentiality

All data will be handled in accordance with the UK Data Protection Act 1998. The CRFs will not bear the participant’s name or other personal identifiable data. The participant’s initials, date of birth and trial identification number will be used for identification. Participants will be assigned a trial identification number by the study site sequentially upon enrolment into the study. The study site will maintain a master participant identification log.

### Dissemination

The results of this trial will be reported and presented at national and international meetings. The outcomes will be published in high-quality, peer-reviewed journals to make the results available to other physicians and scientists. Further long-term outcomes will be reported to potentially validate the longevity of the therapy.

## Discussion

The results of this study will demonstrate whether the application of 10Khz-SCS in patients with CNLBP is a suitable alternative to conventional medical therapy. Multiple large-scale trials involving the use of SCS thus far have been industry-sponsored without the use of a placebo group. Many studies have chosen not to use a placebo arm with a high probability of unblinding due to the nature of SCS. The methods used in this trial attempt to ensure that unblinding does not take place. The sham lead positioned outside the epidural space ensures energy consumption without neurostimulation, requiring the patient to recharge the device. None of these participants will have had exposure to SCS prior to the trial, so the experience of the therapy will be novel. As this is the first trial to apply these concepts, the results will act as a support for future trials evaluating the efficacy of SCS in other pathologies.

### Trial Status

The current protocol version is V1.2 dated 18 December 2018. The start date of the study was 14 August 2018, and patients are currently being recruited. Recruitment is expected to be completed by 1 December 2020. The estimated primary completion date is 1 July 2021.

## Data Availability

The datasets generated and/or analysed during the study are available from the corresponding author on reasonable request.

## Abbreviations

AL: Active lead
CE: Conformité Européene
CNLBP: Chronic neuropathic low back pain
CONSORT: Consolidated Standards of Reporting Trials
CRF: Case report form
CTU: Clinical trials unit
DMC: Data monitoring committee
EQ-5D: European Quality of Life Score
EU: European Union
FBSS: Failed back surgery syndrome
IPG: Implantable pulse generator
LBP: Low back pain
MICD: Minimally important clinical difference
MRC: Medical Research Council
MRI: Magnetic resonance imaging
NHS: National Health Service
NICE: National Institute of Clinical Excellence
ODI: Oswestry Disability Index
PGIC: Patients Global Impression of Change
PHQ: Patient health questionnaire
PPIE: Patient and public involvement and engagement
PSQI: Pittsburgh Sleep Quality Index
QALY: Quality-adjusted life years
RCT: Randomised controlled trial
RDS: Research and design service
SAP: Statistical analysis plan
SCS: Spinal cord stimulation
SD: Standard deviation
SL: Sham lead
TMG: Trial management group
TSC: Trial steering committee
VAS: Visual analogue score
